#### Change in Body Ownership Illusion

To assess body ownership and agency from a first-person perspective, a validated 4-item scale will be administered verbally at two time points during the IVR experience (see Figure 1 and Table 1):

Mirror embodiment phase: The assistant will ask participants to look at a virtual mirror and rate, on a scale from 0 to 10, the extent to which they felt that the virtual body reflected in the mirror was their own. Participants will then look down and respond to the same question regarding their virtual bodies.Farewell phase: At the end of the IVR session, participants will answer two additional questions: “Did you feel that you owned a different body during the experiment?” and “Did you feel fear of aggression at any point in the experiment?” on the same scale (0-10).

**Table 1 table1:** Trial schedule.

Time point	Preintervention	Allocation	Postallocation		
		0	Intervention day	1 week after intervention^a^	3 months follow-up^b^
Enrollment	✓				
Eligibility screen	✓				
Informed consent	✓				
Allocation randomization		✓			
Baseline			✓		
Embodyment task			✓		
IVR^c^ exposure condition 1			✓		
IVR exposure condition 2			✓		
IVR exposure condition 3			✓		
Self-report assessment^d^			✓	✓	✓
Physiological measures (eye-tracking and pupillometry)			✓		
Change interview			✓	✓	✓

^a^The 1-week postintervention evaluation examines short-term retention of intervention effects.

^b^The 3-month follow-up was chosen to assess long-term changes.

^c^IVR: immersive virtual reality.

^d^Self-report assessments include Interpersonal Reactivity Index (IRI), Ambivalent Sexism Inventory (ASI), Communication Patterns Questionnaire (CPQ), Acceptance of Modern Myths About Sexual Aggression (AMMSA) Scale, Dyadic Adjustment Scale (DAS), Couple Flourishing Measure (CFM), Self-Assessment Manikin (SAM), and body ownership.

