### Intervention Procedure

The intervention follows 5 phases, as shown in Figure 1. Each participant will arrive at the laboratory and provide their consent to participate in the study. They will be randomly assigned; participants will be naïve to the study hypotheses. While avatar creation takes place, the couple will answer preintervention questionnaires. Phase 1 also involves the process of personification of the avatar according to the condition in which they will be assigned (see the section on the Intervention Description).

During phase 2, the participants will perform a mirror embodiment task to familiarize themselves with the virtual environment and their new virtual body. More specifically, a female virtual assistant will welcome the participants and instruct them to perform some physical body movements while observing themselves in a virtual mirror. The observation of real-time movements in the embodied avatar, which corresponds to the participants’ real body movements, will allow for greater immersion, as well as enhance body ownership and agency toward the virtual body. For assessment purposes, the female assistant will be a sexualized avatar. During this initial outreach, eye-tracking data will be collected from the participants in relation to the assistant’s cleavage, as gaze fixation on sexualized body parts has been identified as a marker of sexual objectification [47,52]. Once the training and embodiment process is completed, participants will be asked the first questions related to embodiment to check the degree of embodiment achieved.

In phase 3, men will have a 180-second adaptation period in which they will be in an empty bar, and nothing will happen, while women will be in a neutral playful setting in all 3 conditions. Condition 1 men will be involved in a situation of sexual harassment by a group of other men (eg, unwanted flirting, verbal intimidation, and sexist comments). In condition 2, they will stay the same length of time as in the other conditions, but in this case, they will not be sexually harassed. Finally, those in condition 3 will witness the same harassment as in condition 1, but from a bystander perspective, that is, the assaulted person will be a random virtual woman. While people are exposed to the scenarios, their emotional arousal will be assessed by pupillometry in the 3 experimental conditions; however, SAM will be used at the end of phase 3.

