Phase 4 will be similar for the 3 conditions. In condition 1, men will have a virtual meeting with their partners (both still with the exchanged identity) outside the context in which the harassment situation occurred. The man will be asked to recount his experience related to the harassment experienced virtually to his partner, who will then be asked to respond empathetically. In condition 2, participants will also meet with their partners (maintaining the virtual identity exchange) outside the scenario in which they were and will be asked to discuss their concerns and expectations of the relationship related to gender issues. In condition 3, participants will discuss the sexual harassment they witnessed in the bar scene, while embodying their own avatar (not exchanged). This discussion will emphasize their reflections on the observed behavior and its consequences, promoting personal insights from their perspective as bystanders.

In phase 5, the sexualized female avatar will appear to perform the farewell, and the participants’ gaze will be traced. Before the end, two questions related to body belonging will be asked. Outcome assessments will be conducted immediately after the intervention (posttest) and at 3 months (follow-up).

The intervention will be discontinued for a participant if they experience severe cybersickness (eg, nausea, dizziness, and disorientation), acute psychological distress, or technical failures that compromise the integrity of the experience or data collection. Participants will be informed that they may request to stop the session at any time without providing a reason. In such cases, the session will be immediately terminated, and appropriate support will be offered if needed.

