#### Quantitative Analysis

##### Primary Analysis

The primary outcome is the change in beliefs related to sexual aggression. The primary comparison of interest is the condition × time interaction—specifically, whether change from baseline to postintervention and from baseline to 3-month follow-up differs across the 3 experimental conditions (IVR-based intervention, control condition A, and control condition B). This will be estimated using a single prespecified linear mixed-effects model with fixed effects for condition (3 levels, dummy-coded), time (3 levels, with baseline as reference), and their interaction, and random intercepts for couples and for participants nested within couples. The female partner’s scores (eg, Dyadic Adjustment Scale and Couple Flourishing Measure) will be included as covariates to control for baseline relationship quality. This model structure was selected as the primary analytic approach; ANOVA-based omnibus tests and simpler regression models will not serve as primary analyses but may be reported descriptively.

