##### Couple-Level Dependence

Because participants are recruited and randomized as couples, observations within a dyad are nonindependent. This clustering is addressed through the inclusion of couple-level random effects in all mixed-effects models. As a sensitivity analysis, generalized estimating equations with an exchangeable working correlation structure (*geepack*) will also be estimated to obtain population-average intervention effects.

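### The primary model gives the immediate and 3-month contrasts one common standard error despite unequal gaps, and it does not use the baseline score to gain precision

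*Protocol article*

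**What the plan says.** The Primary Analysis section specifies "fixed effects for condition (3 levels, dummy-coded), time (3 levels, with baseline as reference), and their interaction, and random intercepts for couples". The same sentence extends the intercepts to individuals: "and for participants nested within couples". It calls this a single prespecified model and adds: "This model structure was selected as the primary analytic approach". The quantity of interest is "whether change from baseline to postintervention and from baseline to 3-month follow-up differs across the 3 experimental conditions". The covariates named are the female partner's relationship scores; the man's own baseline AMMSA score is not among them. No random slope, residual correlation or visit-specific variance is stated.

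On timing, the Intervention Procedure section places baseline at the laboratory visit ("While avatar creation takes place, the couple will answer preintervention questionnaires"), the posttest directly after the session and follow-up at 3 months. The overview of the experimental design gives the main session as 1 hour. Table 1 instead ticks self-report on the intervention day, at 1 week and at 3 months, with the note "The 1-week postintervention evaluation examines short-term retention of intervention effects".

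The Couple-Level Dependence section adds, as a sensitivity analysis only, "generalized estimating equations with an exchangeable working correlation structure". It does not say which type of standard error will be used.

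**The concern.** There are two separate issues, and both follow from the stated model.

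First, a random intercept gives any two visits of the same man the same correlation, and every visit the same variance. This holds whether the model contains the men only or both partners. Answers to the same 30-item scale on one day may well agree more closely than answers 3 months apart. If so, the model averages two different error variances and applies the average to both contrasts, so neither confidence interval has its stated coverage.

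Second, the condition main effect leaves the baseline means free in each arm. Covariates that are constant over time cancel out of change-from-baseline contrasts, so the partner's scores do not help. With complete data, the interaction coefficient is the plain difference in change scores. If baseline is measured before allocation, randomisation makes the true baseline means equal, and the model discards that information. With 30 men per arm the loss is worth avoiding.

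**Working it through.** **The plan's own figure.** The Sample section gives 84 couples for d = 0.4, power 0.9 and alpha .05. Two readings reproduce 84:
- a 3-group by 2-time interaction with f = 0.2 and r = 0.5, noncentrality 0.2² × 84 × 2/(1 − 0.5) = 13.44;
- a one-way ANOVA with f = 0.4, noncentrality 0.4² × 84 = 13.44.

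Both have 2 and 81 degrees of freedom, so the stated figure cannot show whether a correlation of 0.5 was assumed or none at all. The section itself says that the repeated-measures structure was not modelled. The correlations below are therefore assumptions.

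**Common standard error.** Inputs: n = 30 per arm (Sample section), one man per couple, equal variances, complete data, SD units. Let r01, r02 and r12 be the baseline-post, baseline-3-month and post-3-month correlations, and rbar their mean.
- Model SE, both contrasts: sqrt((2/n) × 2 × (1 − rbar))
- True SE of a contrast: sqrt((2/n) × 2 × (1 − r0k))
- Ratio, model to true: sqrt((1 − rbar)/(1 − r0k))
- Actual two-sided alpha: 2 × (1 − Φ(1.96 × ratio))

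Example, 0.80/0.70/0.70: rbar = 0.7333 and model SE = sqrt(0.1333 × 0.2667) = 0.189. The true SE is sqrt(0.1333 × 0.20) = 0.163 at post and sqrt(0.1333 × 0.30) = 0.200 at 3 months.

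| r01/r02/r12 | ratio, post | ratio, 3 months | alpha, post | alpha, 3 months |
|---|---|---|---|---|
| 0.70/0.70/0.70 | 1.00 | 1.00 | 0.050 | 0.050 |
| 0.80/0.70/0.70 | 1.15 | 0.94 | 0.024 | 0.065 |
| 0.90/0.60/0.65 | 1.68 | 0.84 | 0.001 | 0.10 |
| 0.70/0.70/0.80 | 0.94 | 0.94 | 0.065 | 0.065 |
| 0.60/0.70/0.70 | 0.91 | 1.05 | 0.074 | 0.039 |

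In the third row, post power for 0.4 SD is Φ((0.4 − 1.96 × 0.1944)/0.1155), about 56%. A correct standard error would give Φ(0.4/0.1155 − 1.96), about 93%.

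For the omnibus condition-by-time test, simulation (40,000 trials per setting) with r01 of 0.80 to 0.90 and the other two correlations 0.60 to 0.70 gave an actual alpha of about 0.054 to 0.072.

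**Free baseline means.** The baseline-adjusted SE is sqrt((2/n) × (1 − r²)). The change-score SE divided by this is sqrt(2(1 − r)/(1 − r²)) = sqrt(2/(1 + r)): 1.118 at r = 0.6, 1.085 at 0.7 and 1.054 at 0.8, an inflation of about 12%, 8.5% and 5%.

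At r = 0.7 the change-score SE is sqrt(0.0667 × 0.6) = 0.200 and the adjusted SE is sqrt(0.0667 × 0.51) = 0.184. Power for 0.4 SD is about 51% against 57% with a t reference on about 87 degrees of freedom (52% against 58% with the normal approximation).

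**The case against.** A reader might infer that the 3-month test is certainly anticonservative and the immediate test certainly underpowered. The document does not support that. It gives no between-visit correlation and no AMMSA standard deviation. A session meant to shift beliefs, with varied response, could lower the baseline-post correlation and reverse the direction, and unequal visit variances would also matter. If the 1-week assessment in Table 1 is the post measure, a correlation near 0.90 is harder to defend. The omnibus interaction test is distorted less than the single 3-month contrast in the extreme setting. All of this stands, and it is why the result is given as a range.

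It can also be said that nlme is listed in the Data Analysis Plan and can fit a residual structure, and that an article may leave this to a fuller plan. That stands only in part: the structure is named and fixed as primary, and nothing in it signals an additional residual covariance. An exchangeable working correlation in the GEE is no fault in itself if robust standard errors are used, but the GEE is not the primary analysis.

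Last, free baseline means might be read as a source of bias. They are not: with complete data the difference in change scores is unbiased and valid. This part concerns efficiency only. Free means are even the cautious choice if baseline is taken after allocation, and the document is unclear on that. The Sample section conceals allocation until baseline is complete, whereas the Intervention Procedure section mentions assignment before the questionnaires and Table 1 lists baseline under postallocation.

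**Conclusion.** The point holds in conditional form. As specified, the model gives both primary contrasts one standard error, and it is right for both only if the correlations and variances across visits are in effect equal. If the baseline-post correlation is the highest, the post standard error is too wide and the 3-month one too narrow. Over the two such settings tabulated, this runs from 15% and 6% to 68% and 16%, with 3-month alpha from about 0.065 to 0.10. Under other plausible patterns both are too narrow, or the direction reverses. The loss from free baseline means is modest but present for any correlation below 1: about 5% to 12% in standard error for r from 0.8 to 0.6, or some 6 points of power at r = 0.7.

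All sizes rest on assumed correlations, equal variances, complete data and 30 men per arm. The case for changing the model does not depend on which pattern is true. The change should be made, and the document states that recruitment had not begun.

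**What to change.** For the men's AMMSA score, replace the random-intercept structure with an unstructured covariance across the three visits (for example nlme::gls with corSymm and varIdent) and small-sample degrees of freedom. Either constrain the baseline means to be equal across arms by dropping the condition main effect while keeping the condition-by-time terms at the post-baseline visits, or use baseline AMMSA as a covariate with only the post-baseline visits as outcomes.

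Before that, reconcile the Sample section with the Intervention Procedure section and Table 1, so that baseline is clearly completed before allocation. Also reconcile the immediate posttest with the 1-week assessment in Table 1, because this sets how far the two gaps differ. Keep the GEE as a sensitivity analysis and state that its standard errors are robust.

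The cost is a few lines of R in a package already listed, plus plan wording. The statistical price is four more covariance parameters (6 instead of 2). If the correlations and variances were in fact equal, the residual degrees of freedom would fall from (90 − 3) × 2 = 174 to 87. The critical t would rise from 1.974 to 1.988, which is under 1%.

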## Methods

### Objectives

The primary objective of this randomized controlled trial is to evaluate the efficacy of the REVISE intervention in reducing beliefs that legitimize or minimize sexual aggression (Acceptance of Modern Myths About Sexual Aggression [AMMSA] scale) among heterosexual men at postintervention and at 3-month follow-up.

The secondary objectives are

To evaluate the effects of the REVISE intervention on empathy, gender role attitudes, relationship functioning, and communication patterns.To assess changes in physiological responses (eye tracking and pupillometry) during the IVR experience across experimental conditions.To explore participants’ subjective experiences and perceived changes following the intervention through qualitative interviews, and to integrate these findings with quantitative outcomes.

It is hypothesized that participants exposed to identity-swapping with sexual harassment scenarios will show greater reductions in beliefs legitimizing sexual aggression compared to the control conditions.

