##### Secondary Outcomes

Empathy, gender attitudes, relationship functioning, and physiological responses will each be analyzed using prespecified mixed-effects models with the same fixed-effects structure as the primary model, adapted to the distribution of each outcome (eg, binomial models for binary outcomes and Poisson or negative binomial for count outcomes). Eye-tracking and pupillometry measures collected during IVR exposure will be analyzed using linear mixed-effects models with random intercepts for participant and, where applicable, for stimulus item. Descriptive statistics and effect sizes (Cohen *d* or partial *η*²) with 95% CIs will be reported for all outcomes.

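### The primary mixed model does not say whose AMMSA scores it analyses: its random effects imply both partners and its covariates imply men only, while the objective concerns men

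*Protocol article*

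**What the plan says.** All places are in the Protocol article.

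- **Objectives.** The primary objective is to reduce AMMSA beliefs "among heterosexual men at postintervention and at 3-month follow-up". The Overview of the Experimental Design and the Trial Design section also name heterosexual men as the target.
- **Primary Analysis, fixed effects.** A single prespecified linear mixed model has "fixed effects for condition (3 levels, dummy-coded), time (3 levels, with baseline as reference), and their interaction". No sex or role term is listed.
- **Primary Analysis, random effects.** The model has "random intercepts for couples and for participants nested within couples".
- **Primary Analysis, covariates.** The female partner's "scores (eg, Dyadic Adjustment Scale and Couple Flourishing Measure) will be included as covariates to control for baseline relationship quality".
- **Couple-Level Dependence.** Observations within a dyad are treated as dependent: "This clustering is addressed through the inclusion of couple-level random effects in all mixed-effects models".
- **Sample.** The final sample is counted as 180 individuals in 90 couples, 30 couples per arm.
- **Intervention Procedure.** Both partners complete the baseline questionnaires. In phase 3, "women will be in a neutral playful setting in all 3 conditions". In phase 4 the content of the couple's virtual meeting differs by condition.
- **Secondary Outcomes (analysis).** Empathy, gender attitudes, relationship functioning and physiological responses are modelled "with the same fixed-effects structure as the primary model".

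No section says whose AMMSA scores are the dependent variable.

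**The concern.** The article fixes the outcome, fixed effects, random effects and covariates and calls the model prespecified. The problem is therefore in what is written, not in detail left to a later analysis plan. The stated parts do not describe one model that answers the stated question.

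Two things are at stake. First, followed literally on both partners, the model estimates a couple average, whereas the objective and the intervention's declared target are the male partner. Secondly, whether the primary analysis rests on 90 or 180 people is open, and that choice could end up being made after data have been seen.

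A smaller issue follows from carrying the primary model's structure to the secondary outcomes. If the covariates travel with it, the female partner's DAS and CFM would enter models in which DAS and CFM are the outcomes.

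**Working it through.** **1. The plan's own figure.** The Sample section gives 84 couples for an effect of 0.4, power 0.9 and alpha .05. With one analysed person per couple, this is reproduced in two ways:
- one-way ANOVA, 3 groups, f=0.4: N=83, rounded to 84 for equal arms, power 0.907;
- group-by-time interaction, 3 groups, 2 measurements, f=0.2, assumed correlation 0.5: N=83, rounded to 84.

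Both rest on conventions the article does not state, so they do not settle which rows are analysed.

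**2. Both partners analysed.** Each couple gives one man and one woman, so role is balanced within every arm. Without role interactions the condition x time coefficient is

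(d_men + d_women)/2 = d_men x (1+w)/2, with w = d_women/d_men.

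| w | Fraction of men's effect recovered |
|---|---|
| 0 | 0.50 |
| 0.25 | 0.625 |
| 0.5 | 0.75 |
| 1 | 1.00 |

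Simulation with a true effect of -1 in men gave pooled contrasts of -0.499 (w=0), -0.733 (w=0.5) and -1.008 (w=1), against -0.99 to -1.00 from men alone. A mixed model with both intercepts, fitted to one simulated data set, gave exactly the difference in cell means pooled over sex (-0.440). A sex main effect would not change this, because sex is balanced across arms. The missing term is role x condition x time.

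**3. Pairwise power, 30 couples per arm.** Assumptions not in the documents: baseline-to-follow-up correlation 0.8, within-couple correlation of change 0.3, true effect 0.40 SD in men, w=0.
- Men: SD of change = sqrt(2 x (1-0.8)) = 0.632. SE = 0.632 x sqrt(2/30) = 0.163. Ratio = 0.40/0.163 = 2.45.
- Pooled: SD of the couple's mean change = 0.632 x sqrt((1+0.3)/2) = 0.510. SE = 0.510 x sqrt(2/30) = 0.132. Ratio = 0.20/0.132 = 1.52.

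Simulated power (6000 trials) is 67% in men and 33% pooled. With a visit correlation of 0.9 it is 93% and 57%.

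Pooling stops costing power when (1+w)/2 = sqrt((1+0.3)/2) = 0.806, so w = 2 x 0.806 - 1 = 0.61.

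**4. The same comparison on the plan's 84.** Taking the f=0.4 version (90.7% power in men), the noncentrality is multiplied by ((1+w)/2)^2 x 2/(1+r), where r is the within-couple correlation of change.

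| w | r=0 | r=0.2 | r=0.4 |
|---|---|---|---|
| 0 | 62% | 54% | 47% |
| 0.5 | 94% | 89% | 83% |

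**5. Men only.** Each couple then holds one participant, so the couple and participant intercepts are the same effect and only their summed variance can be estimated. On simulated men-only data the REML log-likelihood was identical (-112.997) for every split of that variance from 0/100 to 100/0, and the fixed-effect estimates did not move.

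**6. Covariates.** Time has three levels including baseline, so the baseline visit is an outcome row. If women's DAS is an outcome and her baseline DAS is also a covariate, that row is predicted by itself.

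**The case against.** **Men only may be what is meant.** The covariate sentence is natural only if the rows are men, the objective names men, and the Intervention Description gives women an observer-report role. This is a fair argument, so the both-partner reading is not settled. It remains the better-supported one: participants nested within couples, couple effects in all mixed models and the count of 180 individuals all point to it. On the men-only reading the harm is small, because the redundant intercept gives an arbitrary variance split or a singular fit and leaves the treatment contrast unbiased.

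**The dilution need not be half.** A reader might infer from the shared neutral phase 3 that women cannot change differently by arm, so that the men's effect is halved. The documents do not support that. In phase 4 the woman in condition 1 hears the harassment account and responds to it, in condition 2 the couple discusses gender issues in the relationship, and in condition 3 the witnessed harassment is discussed. Female partners in condition 1 are also instructed to model empathetic and assertive responses. A small w is plausible but not certain, and at w=0.5 little or no power is lost. This objection stands as a limit on size. It does not remove the mismatch with the objective, which persists unless w=1.

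**The covariates are meant as baseline values.** A reader might infer that a woman's concurrent DAS would absorb her own treatment effect. The stated purpose, "will be included as covariates to control for baseline relationship quality", runs against that. Her baseline DAS in a model of her partner's DAS is ordinary adjustment. It is also arguable that only condition, time and their interaction carry over to the secondary models. What remains is a request for clear wording.

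**Conclusion.** The point holds in a limited form. The primary model is internally inconsistent about whose AMMSA scores it analyses, and on its better-supported reading it does not estimate the effect on men that the objective asks for.

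On both partners, the estimate is (1+w)/2 of the men's effect, a factor of 0.5 to 1.0 for w between 0 and 1. Halving is the end of that range, reached only if AMMSA change in women does not differ by arm. The 33% against 67% comparison depends on w=0 and on assumed correlations, and the power loss is gone at w of about 0.6. On men only, one variance component is redundant and the treatment contrast is sound.

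The correction matters because the ambiguity lies in the single model declared as primary.

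**What to change.** 1. State that the primary estimand is the condition x time effect on men's AMMSA.
2. Estimate it in one of two ways, both valid:
   - men only, one row per man per visit, with a single participant random intercept; or
   - both partners, with role, its two-way interactions and role x condition x time added, keeping the couple and participant intercepts, and with the men's contrast declared primary. Adding a sex main effect alone is not enough.
3. State the number of people in the primary analysis (90 or 180) to match.
4. State that the female partner's DAS and CFM covariates are baseline-visit values, and do not carry a woman's DAS or CFM as a covariate into a model in which that same score is an outcome row.

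The cost is analysis-plan wording. No new data are needed, and the Results section reports that recruitment had not started as of January 2026.

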This study is designed as a randomized, parallel-group, superiority trial with 3 arms and a 1:1:1 allocation ratio. An a priori power analysis was conducted to determine the necessary sample size to detect a meaningful effect in the primary outcome measure. Considering the study design, an estimated effect size of *d*=0.4, statistical power of 0.9, and α level of .05, the required sample size was calculated to be 84 heterosexual couples. To account for potential attrition (estimated at 7%), a total of 90 couples will be recruited. While the a priori power calculation was based on a standard framework, the final sample (N=180 individuals; 90 units of randomization and 30 couples per experimental condition) was increased to provide additional robustness for the planned longitudinal and dyadic analyses. The sample size estimation was based on a conservative effect size derived from prior studies. Although the calculation does not explicitly model the multilevel structure of the data (ie, repeated measures nested within individuals and couples), the use of mixed-effects models in the analysis phase is expected to appropriately account for this dependency structure. The allocation sequence will be computer-generated using random block sizes of 3 or 6 by a research assistant not involved in recruitment, assessment, or intervention delivery. Allocation will be concealed until participant enrollment and completion of baseline assessments (see Figure 1).

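### The covariates named for the primary model cannot move the condition × time estimate, and the baseline AMMSA score is not used to sharpen it: a loss of precision, not a bias

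*Protocol article*

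**What the plan says.** Under Primary Analysis, the article fixes one linear mixed model for AMMSA. It has condition (three levels), time (three levels, baseline as reference), their interaction, and random intercepts for couple and for participant within couple. The comparison of interest is "whether change from baseline to postintervention and from baseline to 3-month follow-up differs across the 3 experimental conditions". The female partner's scores, with DAS and CFM given as examples, "will be included as covariates to control for baseline relationship quality"; no covariate × time term is stated. Baseline AMMSA appears only as the first response level.

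Under Secondary Outcomes in the analysis plan, empathy, gender attitudes, relationship functioning and physiological responses are each modelled "with the same fixed-effects structure as the primary model". DAS and CFM are the satisfaction and flourishing measures, so they are among these outcomes.

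The Sample section gives "an estimated effect size of *d*=0.4", "statistical power of 0.9, and α level of .05", and says that "the required sample size was calculated to be 84 heterosexual couples". No correlation between repeated AMMSA scores is stated.

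**The concern.** Covariates are normally put in a primary model to gain precision or to correct chance imbalance. Here the named covariates can do neither for the comparison that matters. The interaction is a contrast of within-person changes, and a main effect that is constant over time drops out of every such change.

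The baseline value of the outcome is usually the strongest available predictor of follow-up. With a free condition effect at baseline, any chance difference between arms at baseline is subtracted in full. A baseline-adjusted analysis subtracts only the fraction ρ of it, which is more efficient under randomisation. With 30 couples per arm at most, that is worth having, and the data are already being collected.

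**Working it through.** **Inputs.** From the article: 3 arms, 1:1:1, 84 couples before attrition (28 men per arm), 90 recruited, d = 0.4, power 0.9, α .05. Assumed: ρ, the correlation between baseline and follow-up AMMSA, over 0.3 to 0.8; equal variances over time; two-sided tests.

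**1. The plan's own figure.** An F test of group × time with 3 groups, m = 2 time points, f = d/2 = 0.2 and assumed ρ = 0.5 has noncentrality λ = N·f²·m/(1−ρ). For N = 84 this is 84 × 0.04 × 2/0.5 = 13.44, with power 0.907, so the stated 84 is reproduced. A one-way ANOVA with f = 0.4 also gives 84. The article does not say which was used, and the present point does not depend on it.

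**2. Do the named covariates matter?** Write a man's score at time t as (arm and time terms) + β·z + b + e_t, where z is his partner's baseline DAS or CFM and b his random intercept. In the change from baseline to t, both β·z and b cancel. On balanced data the interaction estimate is the difference between arms in mean change, so z cannot enter it.

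Numerical check on simulated data in which DAS truly predicts the outcome:

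| Interaction term | Without DAS, CFM: estimate (SE) | With baseline DAS, CFM: estimate (SE) |
|---|---|---|
| first arm contrast, post | −0.45762 (0.16923) | −0.45762 (0.16923) |
| second arm contrast, post | 0.34235 (0.16923) | 0.34235 (0.16923) |
| first arm contrast, 3 months | −0.40349 (0.16923) | −0.40349 (0.16923) |
| second arm contrast, 3 months | 0.34830 (0.16923) | 0.34830 (0.16923) |

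Only the intercept, the condition main effects and the random-intercept variance moved (the last from 3.60 to 2.95). The interaction estimates were also unchanged with both partners' rows in the model and, for a time-constant covariate, with an exchangeable GEE. Each imputed dataset is balanced, so the identity carries over to the planned multiple imputation. With 7% to 20% dropout at 3 months and no imputation, the estimates moved by at most 0.01 against SEs of 0.17 to 0.19.

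**3. What baseline AMMSA could add.** Per man, in units of the AMMSA variance:

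- change analysis: var = 2(1−ρ)
- baseline-adjusted analysis: var = 1−ρ²
- ratio: (1−ρ²)/[2(1−ρ)] = (1+ρ)/2

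A generalised-least-squares calculation for three arms and three times, with equal correlation ρ between times and a common baseline mean, gives the same ratio at both follow-ups. At ρ = 0.5 and 28 per arm, the contrast variance falls from 0.0714 to 0.0536, a ratio of 0.75.

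| Assumed ρ | Variance ratio | 28 per arm is worth | Two-arm power at 0.4 SD, change → adjusted | Omnibus power at N = 84, f = 0.2 |
|---|---|---|---|---|
| 0.3 | 0.65 | 28/0.65 = 43 | 0.24 → 0.34 | 0.783 → 0.932 |
| 0.5 | 0.75 | 28/0.75 = 37 | 0.31 → 0.40 | 0.907 → 0.969 |
| 0.7 | 0.85 | 28/0.85 = 33 | 0.48 → 0.54 | 0.990 → 0.997 |
| 0.8 | 0.90 | 28/0.90 = 31 | 0.64 → 0.69 | above 0.999 in both |

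The two-arm column takes 0.4 as a pairwise difference in SD units. The omnibus column uses the calculation in step 1, with λ divided by (1+ρ)/2 for the adjusted analysis. Under that calculation at ρ = 0.5, the N for 90% power falls from 84 to 63. Only the increments bear on this point; the absolute power levels depend on how the effect size is read.

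**4. Secondary DAS and CFM models.** If the covariates are carried over, a woman's baseline DAS would be both a response row and a covariate. Simulation gives an unchanged interaction (largest difference 1.6 × 10⁻¹⁴), while the random-intercept variance falls from 0.60 to 0.06. The adjustment is again idle for the contrast.

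**The case against.** The planned model is a standard and unbiased way to compare change from baseline. Baseline AMMSA is not discarded, since it is the reference response, and an idle covariate does no harm to the estimate. All of that stands. So does the point that ρ is an assumption, and that the gain shrinks to 10% of the variance if ρ is 0.8.

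An equal-baseline constraint is justified by randomisation only if baseline is measured before allocation. The article conflicts on this. The Sample section keeps allocation concealed until baseline assessments are complete. Table 1 puts baseline on the intervention day, after the allocation column. Intervention Procedure mentions assignment before the questionnaires, which are filled in while avatars are prepared. If baseline can follow allocation, the free baseline term is the safer choice.

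Two stronger readings are tempting:

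- **Follow-up scores as covariates.** The sentence says scores without the word baseline, so a reader might infer that DAS and CFM enter as time-varying covariates, which would adjust for variables measured after randomisation. In the simulation this moved one estimate from −0.458 to −0.318. The stated purpose, to control for baseline relationship quality, speaks against that reading.
- **Secondary models spoiled by their own outcome.** A reader might infer that the DAS and CFM models condition on the outcome itself. The shared fixed-effects structure may mean only condition, time and interaction. Even if the covariates are copied, baseline values leave the interaction intact, and for men's rows the covariate is the partner's score. Damage would need time-varying scores.

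Finally, DAS and CFM are given as examples, so the covariate list is not closed. A fuller analysis plan may add terms, but the article presents this model as prespecified and single.

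**Conclusion.** The point holds as one of efficiency. Read as baseline main effects, the named covariates contribute nothing to the primary comparison on complete or imputed data. Baseline AMMSA, as a response with a free condition effect, leaves 10% to 35% of the contrast variance to be recovered over assumed ρ of 0.8 down to 0.3. The documents do not support a claim of bias in the primary estimate, or of a secondary analysis invalidated by its own outcome.

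The result rests on the random-intercept linear model as stated, time-constant covariates without a time interaction, equal variances over time, and, for the gain, a baseline taken before allocation. The change is worth making because it is nearly free in a trial limited to 90 couples; the plan is not invalid without it.

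**What to change.** - **Primary model.** Either constrain the arms to a common baseline mean (drop the condition main effect; keep condition × post and condition × 3 months), or take the two follow-up AMMSA scores as the response with baseline AMMSA × time as covariate. Baseline AMMSA should not simply be added to the present model while its baseline rows remain in the response.
- **Baseline timing.** Take baseline before allocation, and reconcile the Sample section, Table 1 and Intervention Procedure on this.
- **Relationship quality.** If it is kept, state that only baseline values enter and add their interaction with time. Without that term the adjustment remains idle.
- **Secondary DAS and CFM models.** Use the same baseline-adjusted form with each outcome's own baseline, and state that the women's follow-up DAS and CFM scores do not enter as covariates.

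The cost is wording in the analysis section, plus settling the order of baseline and allocation. No new data are needed, and the article reports that recruitment had not begun as of January 2026.
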